### 2.3 Study Design

The study will use a multicenter, randomized, double-blind, placebo/active-controlled trial

design.

The study process consists of a screening period, a treatment period, and a follow-up period.

**Screening period: from signing the ICF to randomization, with a maximum of no more than 7 days, and the day of randomization will be recorded as D1.**

The subject will sign the informed consent form and complete the screening according to the study flow chart. The subject will undergo abdominal surgery (laparotomy or laparoscopy) under general anesthesia (total intravenous anesthesia or intravenous-inhalation combined anesthesia). Sevoflurane is selected as inhalation anesthetics, propofol injection is selected as intravenous anesthetics, and the dose of general anesthetics will be determined on an individual basis. Sufentanil injection (0.2-0.6 µg/kg) is selected as opioid analgesics during the anesthetic induction period. Remifentanyl injection (0.1-0.5 µg/kg/min) is selected as opioid analgesics during the anesthetic maintenance period, sufentanil injection (0.1-0.2 µg/kg/time) can be added, and the doses can be adjusted appropriately according to the needs of surgery and the subject's individual conditions. The type and dose of muscle relaxants and other anesthetic adjuvant drugs are at the discretion of the anesthesiologist and/or surgeon. 2.5 µg sufentanil will be intravenously injected immediately ( $\pm$  5 min) after the surgery (the last suture is completed) to prevent postoperative breakthrough pain.

Within 4 hours after the surgery, the investigator will instruct the subjects to assess the pain intensity (PI) at rest using the Numeric Rating Scale (NRS, 0-10 for varying degrees of pain, 0 for painlessness, larger numbers for more severe pain, and 10 for the worst pain), and it is recommended that the interval between the two assessments should not exceed 30 minutes. The subjects with NRS score  $\geq$  4 at rest at any time within 4 hours after the surgery can be randomized (it is recommended to be randomized within 10 min after the NRS score reaches 4 or more for the first time). The subjects will be randomized in a 1:1:1:1 ratio to one of the following groups: SHR8554 Injection 0.75 mg group, SHR8554 Injection 1.0 mg group, morphine hydrochloride injection group, and placebo group.

**Treatment period: from randomization to 24 h, with the time to start infusion of the loading dose of investigational product recorded as 0 h.**

After randomization, the investigator should infuse the investigational product to the subject as soon as possible (within 15 min after the randomization). The loading dose of the investigational product will be 5 mL, administered by an infusion pump, and the intravenous infusion time will be approximately 10 min. The Patient Controlled Analgesia (PCA) pump containing the investigational product can be initiated approximately 30 min after the start of infusion of the loading dose. The subject can receive 1 mL of the investigational product at a single press of PCA pump, and the minimum interval between two adjacent effective presses is 10 minutes. The subject will continue using the PCA pump until 24 h ( $\pm 5$  min).

After the end of loading dose infusion, rescue analgesia may be given if the investigator determines that the investigational product cannot meet the subject's analgesic needs (NRS  $\geq 4$  points). The first choice of rescue analgesics is parecoxib sodium for injection (20 mg for the first intravenous injection, followed by additional doses as needed, with a total dose of not more than 80 mg over 24 h), and sufentanil injection (2.5  $\mu$ g for a single intravenous injection) can be used after reaching the maximum cumulative dose of parecoxib sodium for injection.

After randomization, the investigator will instruct the subject to assess the NRS score at rest within 5 minutes prior to the start of infusion of loading dose as baseline. The investigator will instruct the subject to assess the NRS scores at rest immediately after the infusion and 20 min, 30 min, 45 min ( $\pm 1$  min as the assessment point window from immediately after the infusion to 45 min), 1 h, 1.5 h, 2 h, 3 h, 4 h, 5 h, 6 h ( $\pm 5$  min as the assessment point window from 1 h to 6 h), 8 h, 10 h, 12 h ( $\pm 10$  min as the assessment point window for 8 h, 10 h, and 12 h), 18 h, and 24 h ( $\pm 20$  min as the assessment point window for 18 h and 24 h) after the infusion. At the same time as each assessment of NRS score, the investigator will instruct the subject to assess the degree of pain relief (PR) using the Likert scale (0 as no response, 1 mild response, 2 moderate response, 3 significant response, 4 complete response).

The subject will be required to have continuous ECG monitoring (brief interruptions are allowed due to transit and the subject's necessary activities) from 0 h to stopping the

infusion of investigational product.

The investigator should perform 12-lead ECG and record the subject's vital signs (blood pressure [BP], respiratory rate [RR], heart rate [HR], body temperature [T]) and transdermal oxygen saturation (SpO2) from randomization to 0 h, 1 h, 2 h, 3 h, 6 h ( $\pm 5$  min as the assessment point window from 1 h to 6 h), 12 h, and 24 h ( $\pm 15$  min as the assessment point window for 12 h and 24 h assessments). The investigator will decide whether additional 12-lead ECG is required according to the subject's clinical condition.

During the treatment period, PK blood samples will be collected for plasma concentration analysis and genetic analysis of drug metabolizing enzymes CYP2D6, CYP3A4 and CYP3A5. The time to the first use of rescue analgesics, the cumulative amount of rescue analgesics from the end of the infusion of loading dose to 24 h, the number of treatments of rescue analgesics, the total number of PCA pump presses within 24 h, the number of effective presses of PCA pump, and the time of effective presses of PCA pump will be recorded. Within 30 min after stopping the PCA pump at 24 h ( $\pm 5$  min), the subject and the investigator will score their satisfaction with analgesia of the investigational product, respectively.

**Follow-up period: 24 h to D4  $\pm$  1.**

During the follow-up period, the subject will complete relevant examinations and complete the safety assessment according to the study flow chart.

## 2.4 Sample Size

With reference to the results of the foreign study TRV130-3002, assuming that the primary efficacy variable SPID24 in the SHR8554 0.75 mg group in this study is comparable to the efficacy in the 0.35 mg group in the TRV130-3002 study, and conservatively assuming that the mean (standard deviation) of SPID24 in the low dose group of this study is 88 (45), and the mean (standard deviation) of SPID24 in the placebo group is 70 (40), it's estimated to need 118 subjects in each group by the sample size calculation formula (PASS) of comparing the means of two samples to achieve the power of 90% with  $\alpha = 0.05$  (two-sided), provided that the four groups are designed in a 1:1:1:1 ratio. Considering the

dropout rate of 10%, each group is planned to enroll 132 subjects, with a total of 528 subjects.

## 2.5 Method of Randomization

Using a central randomization method, 528 subjects will be randomized in a 1:1:1:1 ratio to 4 treatment groups: SHR8554 Injection 0.75 mg, SHR8554 Injection 1.0 mg, placebo, and morphine hydrochloride injection.

The random number table will be generated by an unblinded statistician of the statistical team using SAS 9.4, and the blinding will be uniformly completed by an unblinded statistician who does not participate in the study. Randomization will be performed using a central randomization system (Interactive Web Response Randomization System, IWRS). The subjects, investigators, and all personnel involved in the trial or clinical assessment will remain blinded to the true treatment (except the unblinded drug management team) from the randomization until the database is locked.

## 2.6 Blinded Design

The study will be conducted in a double-blind design and subjects who meet the inclusion criteria will be randomized to each treatment group.

The subjects, investigators, and all personnel involved in the trial or clinical assessment will remain blinded to the true treatment (except the unblinded drug management team) from the randomization until the database is locked.

## 2.7 Interim Analysis

NA

## 2.8 Modifications to the Statistical Analysis in the Protocol

NA

# 3. Efficacy Variables

## 3.1 Primary Efficacy Variable

- Time-weighted Sum of Pain Intensity Differences at rest up to 24 h after starting infusion of loading dose of investigational product (SPID24).

### 3.2 Secondary Efficacy Variables

- Time-weighted Sum of Pain Intensity Differences at rest at 6 h, 12 h, 18 h, and 12-24 h (SPID6, SPID12, SPID18, SPID12-24);
- Time-weighted Total Pain Relief at 6 h, 12 h, 18 h, 24 h, and 12-24 h (TOTPAR6, TOTPAR12, TOTPAR18, TOTPAR24, TOTPAR12-24);
- Time to the first use of rescue analgesics;
- Cumulative amount of rescue analgesics from 0 h to 24 h;
- Number of treatments of rescue analgesia from 0 h to 24 h;
- Total number of presses and number of effective presses of PCA pump from 0 h to 24 h;
- Percentage of subjects who do not use rescue analgesics from 0 h to 24 h;
- The subject's satisfaction score with analgesic treatment;
- The investigator's satisfaction score with analgesic treatment.

## 4. Safety Variables

### 4.1 Adverse Events

Treatment-emergent adverse event (TEAE) is defined as any untoward medical condition that occurs after a subject receives the drug, which may manifest as symptoms, signs, diseases, or laboratory abnormalities, but does not necessarily have a causal relationship with the investigational product. AEs include, but are not limited to, the following:

- 1) Worsening of pre-existing (before enrollment) medical conditions/diseases (including worsening of symptoms, signs, laboratory abnormalities);
- 2) Any new AEs: any new adverse medical conditions (including symptoms, signs, newly diagnosed diseases);
- 3) Abnormal and clinically significant laboratory values or results.

The study personnel should record in detail any AE, including: AE name, time of onset,

severity, relationship to the investigational product, end time, action taken with the investigational product, and final results and outcome.

#### 4.2 Treatment-related Adverse Events

The investigator should comprehensively assess and judge the relationship between the AE and the investigational product according to the five-level classification of "related, possibly related, unlikely related, unrelated, not determined". "Related", "possibly related" and "not determined" adverse events are listed as treatment-related adverse events (TRAEs), the sum of which will be the numerator to calculate the incidence of TRAEs, while the number of all subjects for safety evaluation is the denominator.

#### 4.3 Serious Adverse Events

Serious adverse event (SAE) is an event that occurs during the clinical trial that requires hospitalization or prolonged hospitalization, results in disability or incapacity, is life-threatening or fatal, or results in congenital malformations. SAEs include the following medical events:

- Fatal;
- Life-threatening: defined as the subject is at the risk of death at the time of the event rather than assuming a possible death if the condition worsens;
- Requires hospitalization or prolonged hospitalization;
- Leading to permanent or serious disability/incapacity;
- Resulting in congenital anomalies or birth defects;
- Other medically significant events (defined as adverse events that may not immediately result in death, be life-threatening, or require hospitalization, but may jeopardize the subject or require intervention to prevent any of the above outcomes. For example, allergic bronchospasm requiring special treatment in an emergency room or at home, dyscrasia or convulsions that do not result in hospitalization, or development of drug dependence or drug abuse).

#### 4.4 Vital Signs, SpO2 and Physical Examination

- Vital signs: including blood pressure, respiratory rate, heart rate, and body temperature;
- Oxygen saturation (SpO2)
- Physical examination: includes overall appearance, skin and mucosa, lymph nodes, head and neck, chest, abdomen, muscles and bones, nervous system, and other parts of the body.

#### 4.5 Laboratory Tests

- Hematology: including red blood cells (RBC), white blood cells (WBC), neutrophils (NEUT), hemoglobin (HB), platelets (PLT);
- Urinalysis: including urine white blood cells (WBC), urine red blood cells (BLD), urine glucose (U-GLU), urine protein (PRO);
- Blood chemistry: including aspartate aminotransferase (AST), alanine aminotransferase (ALT), total bilirubin (TBIL), creatinine (Cr), fasting or non-fasting blood glucose (FBG or BG), urea nitrogen (BUN) or urea (Urea), potassium (K+), sodium (Na+);
- Coagulation function: thrombin time (TT), activated partial thromboplastin time (APTT), prothrombin time (PT), fibrinogen (Fib).

#### 4.6 12-Lead ECG

- Includes heart rate, PR, QT, and QTc intervals.

### 5. Other Variables

NA

### 6. Analysis Set

The analysis sets include: full analysis set, per protocol set, and safety set.

### 6.1 Full Analysis Set (FAS)

It includes all subjects who received at least one dose of study drug after randomization in accordance with the intent-to-treat (ITT) principle.

Description of baseline demographic data and efficacy evaluation will be performed in the FAS.

Treatment groups will be based on randomization.

### 6.2 Per Protocol Set (PPS)

It is a subset of the FAS and includes the subjects who did not have major protocol deviations in the FAS.

Efficacy analysis of this investigational product will be performed in the FAS and PPS.

### 6.3 Safety Set (SS)

It Includes all enrolled subjects who received the study drug.

This set will be used for safety analysis. Treatment groups will be based on actual grouping.

## 7. Statistical Analysis

### 7.1 General Principles

For continuous variables, the number of non-missing subjects, mean, SD, median, minimum and maximum will be listed. The minimum and the maximum values will be rounded to the same decimal place as the original data recorded in the database. The mean and median values will be rounded to 1 more decimal place than the original data recorded in the database, and the standard deviation value will be rounded to 2 more decimal places than the original data recorded in the database, up to a maximum of four decimal places.

Categorical variables will be listed in a frequency table (frequency and percentage).

Percentages will be rounded to one decimal place.

#### 7.1.1 Test Level

All hypothesis tests will be performed using a two-side test, with  $\alpha = 0.05$ ; if  $P \leq 0.05$ , the differences tested will be considered as statistically significant. All confidence intervals

will use 95% confidence.

### 7.1.2 Hypothesis Testing

The primary efficacy variable of this trial is SPID24, and the difference test will be used for the group comparison between the experimental group and the placebo group.

Hypothesis:

$$H_0: \mu_T = \mu_C$$

$$H_1: \mu_T \neq \mu_C$$

$\alpha$  level: 0.05 (two-sided).

$\mu_T$ : mean SPID24 in the experimental group;

$\mu_C$ : mean SPID24 in the placebo group.

In this study, the high and low dose groups will be tested sequentially to ensure that the Type I error rate  $\alpha$  is controlled within 0.05 (two-sided). The test between the high dose group and the placebo group will be performed first with  $\alpha$  of 0.05 (two-sided). If there is a significant difference between the high dose group and the placebo group, then the test between the low dose group and the placebo group will be performed with  $\alpha$  of 0.05 (two-sided); if there is no significant difference between the high dose group and the placebo group, only exploratory analysis will be performed for the comparison of the low dose group and the placebo group. For the morphine group, only descriptive statistics will be applied.

### 7.1.3 Estimation of Missing Values

For the pain intensity (PI) score, if the subject does not have the PI score during night sleep, NRS = 3 will be uniformly used for imputation;

For the pain relief (PR) score, if the subject does not have the PR score during night sleep, the previous PR score will be uniformly used for imputation.

Regarding the scores after rescue analgesia, within 6 h after rescue analgesia with parecoxib sodium and within 2 h after rescue analgesia with sufentanil, PI/PR scores at pre-specified time points will be imputed using the PI/PR scores before rescue analgesia.

In other cases, missing PI and PR scores will be imputed using the last observation carried forward (LOCF) method.

Missing values in other secondary efficacy variables and safety evaluations will not be estimated.

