### **Emergency Unblinding**

If the treatment grouping information must be unblinded during the study due to urgent management of SAE, or to decide the subsequent treatment, the site should promptly notify the sponsor of the reasons for unblinding, and the principal investigator should submit an

application for unblinding. If the investigational product is unblinded, the sponsor, the investigator at each site and the Ethics Committee must be notified as soon as possible. The unblinding time, reason and results must be recorded in the source documents. If any centrally blinded personnel become aware of the investigational product information (unblinding), the use of the investigational product should be discontinued immediately and the subject must be withdrawn from the study.

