**Withdrawal by the Subject**

1. Subjects may withdraw from the study at any time.
2. The investigator may decide to discontinue the investigational product and/or withdraw the subject from the study if any medical condition occurs prior to dosing or during the administration, which may put the subject at risk, or if the subject is unable to complete the study as specified in the protocol.

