### **Procedures for Subject Withdrawal from the Study**

Every effort must be made to complete the efficacy and safety tests specified in the protocol at the time of withdrawal from the trial, complete the safety follow-up period, and fully record AEs and outcomes. The investigator may suggest or provide new or alternative treatments to the subject according to the subject's actual condition.

If a subject refuses to come to the study site for further visits, his/her AE and outcome should continue to be followed unless the subject withdraws consent to disclose further information or to be contacted. In such cases, no further study evaluations should be performed and no further data should be collected. The sponsor may retain and continue to use all data prior to withdrawal of informed consent by the subject.

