### **Data Analysis/Statistical Method**

#### **Sample Size**

With reference to the results of the foreign study TRV130-3002, assuming that the primary efficacy variable SPID24 in the SHR8554 0.75 mg group in this study is comparable to the efficacy in the 0.35 mg group in the TRV130-3002 study, and conservatively assuming that the mean (standard deviation) of SPID24 in the low dose group of this study is 88 (45), and the mean (standard deviation) of SPID24 in the placebo group is 70 (40), it's estimated to need 118 subjects in each group by the sample size calculation formula (PASS) of comparing the means of two samples to achieve the power of 90% with  $\alpha = 0.05$  (two-sided), provided that the four groups are designed in a 1:1:1:1 ratio. Considering the dropout rate of 10%, each group is planned to enroll 132 subjects, with a total of 528 subjects.

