### 7.5 Sensitivity Analysis

- Time-weighted Sum of Pain Intensity Differences at rest up to 24 h after starting infusion of loading dose of investigational product (SPID24). (Score not imputed after rescue analgesia)
- Time-weighted Sum of Pain Intensity Differences at rest up to 24 h after starting infusion of loading dose of investigational product (SPID24). (Randomized population)

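### LOCF also fills pain scores missing after withdrawal for an adverse event or lack of efficacy, and no planned sensitivity analysis tests it

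*Combined protocol and SAP*

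**What the plan says.** The protocol (Handling of Missing Data) leaves imputation to the SAP. SAP 7.1.3 has three layers:

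- Night sleep: "if the subject does not have the PI score during night sleep, NRS = 3 will be uniformly used for imputation". For pain relief, the previous score is used.
- Rescue: for 6 h after parecoxib and 2 h after sufentanil, "PI/PR scores at pre-specified time points will be imputed using the PI/PR scores before rescue analgesia".
- Everything else: "In other cases, missing PI and PR scores will be imputed using the last observation carried forward (LOCF) method".

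The third layer does not depend on why the score is missing. SAP 6.1 keeps every randomised and dosed subject in the full analysis set.

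The protocol has three texts on leaving treatment or the study. Under Withdrawal by the Subject: "The investigator may decide to discontinue the investigational product and/or withdraw the subject from the study". Under Emergency Unblinding, if centrally blinded personnel learn the treatment: "the use of the investigational product should be discontinued immediately and the subject must be withdrawn from the study". Protocol section 6.6, on withdrawal procedures, asks for assessments on leaving: "Every effort must be made to complete the efficacy and safety tests specified in the protocol at the time of withdrawal from the trial". None says whether pain scoring continues to 24 h.

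The sample size section allows for some loss: "Considering the dropout rate of 10%, each group is planned to enroll 132 subjects". SAP 7.5 lists two sensitivity analyses of SPID24. One is labelled "Score not imputed after rescue analgesia"; the other uses the randomised population. The first changes the rescue rule and the second the population, so LOCF stays in both. The per-protocol analysis drops subjects with major deviations but does not change how the remaining subjects are imputed.

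**The concern.** LOCF after withdrawal assumes that relief at the last score would have continued unchanged to 24 h. For a subject who leaves because of an adverse event with pain well controlled, that is generous: the hours after the product is stopped are scored as if its effect persisted. The Phase 1 study (SHR8554-101, PK) reports mean half-lives of 6.08 to 6.96 h, so 20 h after stopping is 20/6.96 = 2.9 to 20/6.08 = 3.3 half-lives.

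The timing of the assessments makes late gaps costly. SAP 7.3.1 weights each score by the planned interval before it, so the 18 h and 24 h scores carry 6 h each, 12 of the 24 h. The other SPID variables and TOTPAR use the same imputation rule.

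At stake is whether the confirmatory comparison with placebo depends on an assumption that the plan never tests. The SAP defines no estimand that would settle how such withdrawals should count.

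**Working it through.** **Planned figure.** Inputs from the protocol's Sample Size section: SPID24 mean (SD) 88 (45) on low dose and 70 (40) on placebo, two-sided alpha 0.05, power 90%.

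n = (45² + 40²) × (1.960 + 1.282)² / 18² = 117.56, so 118 per arm. 118 / 0.90 = 131.1, so 132 per arm and 528 in total. The plan's figures reproduce. Power with all 132 per arm is 93%.

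**One subject.** Relief is counted as positive, in line with the positive planning means. Baseline 6, last score 2 at 6 h, then withdrawn without further scores. LOCF sets the 8, 10, 12, 18 and 24 h scores to 2.

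- Carried weight: 2 + 2 + 2 + 6 + 6 = 18 h.
- LOCF credit: 4 × 18 = 72 points.
- Credit at the average placebo PID: (70/24) × 18 = 52.5 points, so the excess is 19.5.
- Credit under baseline carried forward: 0 points, so the excess is 72.

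**Group level.** Average PID implied by the plan: 88/24 = 3.67 active, 70/24 = 2.92 placebo. Assume that lost subjects have no scores after 4 h (20 h carried) and that their last score equals their arm's average.

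- LOCF credit: 3.67 × 20 = 73.3 active, 2.92 × 20 = 58.3 placebo.
- Excess over placebo-based imputation: 73.3 − 58.3 = 15 per active subject lost, and on average 0 per placebo subject lost.
- Inflation against placebo-based imputation = q_A × 15.
- Inflation against zero credit = q_A × 73.3 − q_P × 58.3.

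The rates q_A and q_P are assumptions; the documents give none.

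| Lost, active / placebo | Against placebo-based | Against zero credit |
|---|---|---|
| 2% / 0% | 0.3 | 1.5 |
| 5% / 0% | 0.75 | 3.7 |
| 10% / 0% | 1.5 | 7.3 |
| 10% / 5% | 1.5 | 4.4 |
| 10% / 10% | 1.5 | 1.5 |
| 0% / 5% | 0 | −2.9 |

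As a share of 18 points, the 10% / 0% row is 8% or 41%, and the 2% / 0% row is 2% or 8%. The last row shows that the sign can reverse.

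**Cost of zero credit as the primary rule.** Assume that 18 points is the LOCF result and that loss occurs after 6 h, so the active credit is 3.67 × 18 = 66.

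- At 10% / 0% the difference is 18 − 0.10 × 66 = 11.4. A lost subject keeps 6/24 of SPID24, so the active mean is 88 × 0.925 = 81.4. The variance is 0.90625 × (45² + 88²) − 81.4² = 2227, giving an SD of 47.2. The standard error is √((2227 + 1600)/132) = 5.385. Power is Φ(11.4/5.385 − 1.960) = 56%.
- At 2% / 0% the difference is 18 − 0.02 × 66 = 16.7 and power is about 88%.

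**The case against.** The strongest reply is that the effect may be negligible. In Phase 1 no adverse event led to withdrawal. In the Phase 2 study (SHR8554-201P) one subject in 51 withdrew for an adverse event, on morphine, and none of the 30 on SHR8554 did. Drug-related adverse events there were more frequent on placebo (80%) than at the two retained doses (50% and 70%). Those studies are small, but they are the only evidence in the documents. This stands: neither the direction nor the size of the bias can be established from the documents.

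Four stronger readings are tempting and are not supported.

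- A reader might infer that stopping the product triggers LOCF. It does not; a missing score does. The protocol separates stopping the product from leaving the study, and a subject who stops but is still scored contributes observed data. If rescue follows, the rescue rule applies for its window, and a score missing through night sleep becomes 3.
- A reader might infer that the SAP contradicts itself by denying credit after rescue and granting it after withdrawal. Both rules carry a score from before the event. Rescue scores are poor because rescue requires NRS ≥ 4, and LOCF likewise carries a poor score for someone who leaves in pain.
- A reader might take the 10% dropout figure as a rate of adverse-event withdrawal. It is an all-cause planning allowance.
- A reader might conclude that some 40% of the planned effect is artefact. That needs 10% loss on active, none on placebo, and zero credit as the benchmark. Zero credit is strict, since the plan expects placebo subjects to average a PID of 2.92.

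What survives the reply is that the assumption goes untested.

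**Conclusion.** The point holds in limited form. LOCF applies to scores missing after withdrawal for an adverse event or lack of efficacy, and nothing in SAP 7.5 examines it. A subject who leaves with a low score can be credited with several times the planned 18-point difference for unobserved hours.

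At group level the inflation is about 0.3 to 1.5 points against placebo-based imputation, for 2% to 10% active loss after 4 h. Against zero credit, with no placebo loss, it is 1.5 to 7.3 points. These figures rest on assumed rates and timing and on last scores equal to the planned averages. The bias favours SHR8554 only if such withdrawals are more frequent on active drug or have better last scores than on placebo. The sample size is not in dispute.

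This should be fixed because the fix is cheap and the primary endpoint is affected. The documents do not show that the trial's conclusion is at risk.

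**What to change.** 1. State in the protocol that scheduled NRS and pain-relief scoring continues to 24 h after the investigational product is stopped, unless consent is withdrawn, and in the SAP that these observed scores are used. Reconcile this with Emergency Unblinding, Withdrawal by the Subject and Procedures for Subject Withdrawal from the Study. For unblinded subjects, say whether later self-reported scores count, since knowledge of treatment may colour them. This concerns data collection only, not when the product should be stopped.
2. In SAP 7.1.3, for scores still missing after withdrawal for an adverse event or lack of efficacy, replace LOCF by multiple imputation based on the placebo arm. Keep LOCF for isolated gaps, and state the order in which the sleep, rescue and withdrawal rules apply.
3. In SAP 7.5, add full LOCF and baseline carried forward as sensitivity analyses. Baseline carried forward fits better here than as the primary rule, given the power loss shown above.

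At minimum, add one sensitivity analysis that does not use LOCF for these withdrawals.

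The cost is a few sentences of protocol and SAP text, a little more analysis work, and possibly a slightly smaller estimated effect.
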